### Secondary outcomes

Auditory Verbal Learning Test (AVLT) is one of the most commonly used memory assessment scales. In this study, the Chinese version of AVLT developed by Guo Qihao et al. [36] was adopted. The scale uses 12 words. During the test, the examiner reads the 12 words aloud, and participants are asked to recall them immediately. They continuously learn and recall the words three times, with reminders provided beforehand. After an approximately 5-minute non-verbal test interval, participants perform “short delayed recall” of the words, and after a 20-minute interval, they perform ‘long delayed recall’. The sixth recall is re-recognition, where the examiner presents 24 words and asked the subjects to identify which were learned.

The Animal Fluency Test (AFT) is used to assess a patient’s language function [37]. Participants list as many animals as possible within 60 s, with each correctly named animal counting as one point. A higher score indicates better language function.

The Clock Drawing Test (CDT) primarily assesses a patient’s visuospatial function. Participants draw a clock on a blank sheet, adding numbers and setting the hands to 11:10. The scoring method follows the Rouleau 10-point scale: clock face integrity (maximum 2 points), presence and sequencing of numbers (maximum 4 points), and presence and placement of the hands (maximum 4 points) [38].

The Shape Trails Test (STT) was developed by the U.S. Army in 1944 as part of the Halstead-Reita suite of neuropsychological tests. This study uses a version by Guo Qihao et al. [39]. The test has two parts, A and B, involving two shapes: square and circle. STT-A requires connecting numbers, assessing attention and processing speed with a maximum of 150 s. STT-B involves alternating connections of shapes, evaluating executive function with a maximum of 300 s. For both tests, shorter completion times indicate better performance.

The Modified Barthel Index (MBI) [40] assesses activities of daily living (ADLs), covering ten areas: feeding, dressing, toileting, personal hygiene, bathing, bed-chair transfer, walking, stair climbing, bowel control, and bladder control. A score of ≤40 indicates severe dependency, 41 to 60 implies moderate dependency, 61 to 99 reflects mild dependency, and 100 signifies normal activity without assistance.

The Neuropsychiatric Inventory-Questionnaire (NPI-Q) is used to assess neuropsychiatric symptoms [41]. It consists of 10 behavioral and 2 autonomic nervous system symptom domains. Researchers gather information about symptoms over the past month from caregivers. Symptoms are marked “present” if they occurred and rated for severity (0–36 points) and caregiver distress (0–60 points). The Chinese version of the scale has a Cronbach’s α of 0.85, split-half reliability of 0.83, and test-retest reliability of 0.86 [42].

This study uses the short form of the Center for Epidemiologic Studies Depression Scale (CES-D), comprising 9 items: 2 positive and 7 negative symptoms. Internal consistency reliability ranges from 0.85 to 0.88. Scoring reverses positive symptoms, with a total of 27 possible points. A score of 10 indicates a tendency toward depression, while 17 marks the high-risk threshold [43].

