**Methods:**

This study is a dual-arm, single-center, single-blind, randomized controlled trial. A total of 86 AIS patients will be enrolled and randomly assigned in a 1:1 ratio to either the intervention group or the control group. The control group will receive conventional exercise education and follow-up. The intervention group first watched tactile stimulation followed by TC action videos, and then practiced imitating TC movements. The program will be implemented once a day for 30 min, 5 days a week for a duration of 8 weeks. Outcome measures will be assessed at baseline, week 8, and week 12. The primary outcome is global cognitive function and secondary outcomes are language, attention, executive function, memory, visuospatial ability, neuropsychological assessments, and quality of daily life.

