### Eligibility criteria

#### Inclusion criteria

The first stroke was in accordance with the Chinese guidelines for diagnosis and treatment of acute ischemic stroke 2023 [31] and was confirmed by brain CT or MRI.First onset of stroke, with disease duration of less than 14 days;The NIHSS score less than 5;Muscle strength of limbs > level 3.

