### Interventions

In this prospective, two-arm, single-centre, randomized controlled trial study, we will recruit 86 acute ischemic stroke patients within 14 days of onset. Participants will be randomly assigned to either an intervention group (receiving TC-AOT combined with SOT) or a control group (undergoing routine cognitive rehabilitation) in a 1:1 ratio. All patients will receive routine treatment and conventional exercise education, delivered by professional therapists during hospitalization. After discharge, education and follow-up will be conducted by our medical and nursing team. Additionally, in the intervention group, patients will begin by watching a sensory activation video, followed by watching a video on 8 Trigram 5 Steps TC, and then engaging in TC exercises. The program will be implemented once a day for 30 min, 5 days a week, and will last for 8 weeks. Based on the results of the preliminary literature review and evidence-based analysis, and after an expert panel meeting, the interventions were ultimately developed as illustrated in Figure 2.

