### Outcomes

At baseline, patients will undergo the AD8 test to screen for pre-stroke cognitive impairment; those identified with such impairment will be excluded. Routine sociodemographic data will also be collected, including age, gender, marital/cohabitation status, employment status, as well as personal and family medical history, and smoking and alcohol consumption habits.

Validated assessment tools will be employed to evaluate global cognitive function, memory, language function, executive function, attention, visuospatial ability, activities of daily living, neuropsychiatric symptoms, and psychological status. Each scale will be analysed independently, no composite total score will be calculated across different scales.

Subjects will be evaluated at three time points: before the intervention (1–2 days before the start, T1), after the intervention (1–2 days following the 8-week intervention, T2), and during follow-up (4 weeks after the 8-week intervention, T3). The safety outcome, particularly the incidence of falls, will be monitored throughout the study.

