### Data analysis

A statistician will analyse the data using SPSS 26.0 software, considering a P-value < 0.05 as statistically significant. Continuous variables will be presented as mean ± standard deviation or median with interquartile range, while categorical variables will be expressed as frequency and percentage. The outcome measures in this study are all continuous variables. Differences in outcomes at baseline, week 8, and week 12 will be analysed using repeated measures ANOVA or mixed linear regression analysis. Both the intention-to-treat (ITT) and per-protocol (PP) populations will be included in the analysis. The ITT and PP analysis results will be compared to ensure consistency. In cases of missing data, the last observed value will be carried forward for interpolation. A safety analysis will be performed to assess safety outcomes.

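### The one-month NPI-Q recall makes the T1 window largely pre-stroke, so T1 is better used as a covariate than as a time level, and change from T1 is not post-stroke change

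*Protocol article*

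**What the plan says.** All places are in the protocol article.

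- **Recall period.** Secondary outcomes, on the NPI-Q: "Researchers gather information about symptoms over the past month from caregivers". A symptom is scored as present if it occurred in that period, and is then rated for severity and caregiver distress. No other period is given for T1.
- **Entry.** Inclusion criteria: "First onset of stroke, with disease duration of less than 14 days". Interventions repeats it: "we will recruit 86 acute ischemic stroke patients within 14 days of onset".
- **Timing.** Outcomes places T1 1–2 days before the programme starts, T2 1–2 days after the 8 weeks end, and T3 4 weeks after they end. The abstract makes no exception for any scale: "Outcome measures will be assessed at baseline, week 8, and week 12".
- **Analysis.** Data analysis: "Differences in outcomes at baseline, week 8, and week 12 will be analysed using repeated measures ANOVA or mixed linear regression analysis". Baseline is thus one of the time points analysed, for the NPI-Q as for the other scales.

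**The concern.** A one-month look-back from a visit less than two weeks after a stroke reaches back before the stroke. The same question at T2 and T3 covers only time after it. The three NPI-Q scores therefore refer to different kinds of period, yet the plan analyses them as one measure at three times.

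Two things are at stake. The first is interpretation. A shift from T1 to T2 mixes real change in post-stroke symptoms with the loss of symptoms confined to pre-stroke days and with a longer post-stroke period in which a symptom can occur. The second is precision. A T1 score that partly refers to another period may correlate less with follow-up. If the arm effect is then read as a difference in change, a weak baseline inflates its variance.

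**Working it through.** The document states no figure for this point, so there is none to reproduce.

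**Step 1. Share of the T1 window that precedes the stroke.** Inputs: a recall window of W days (one month, so 28 to 31) and d days from onset to T1 (entry is under 14 days). Share = (W − d)/W.

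| d | W = 28 | W = 30 | W = 31 |
|---|---|---|---|
| 1 | 96% | 97% | 97% |
| 3 | 89% | 90% | 90% |
| 7 | 75% | 77% | 77% |
| 10 | 64% | 67% | 68% |
| 13 | 54% | 57% | 58% |
| 14 | 50% | 53% | 55% |
| 16 | 43% | 47% | 48% |

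For d from 1 to 13 the share runs from 15/28 = 54% to 30/31 = 97%. It falls to half or less only from about day 14 to 16.

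**Step 2. The T2 and T3 windows.** T2 is 56 + 1 to 2 = 57 to 58 days after the programme starts. A 31-day window from day 57 reaches back to day 57 − 31 = 26. T3 is at about 56 + 28 = 84 days, and its window reaches back to day 84 − 31 = 53. Both windows begin after the programme starts, and so after the stroke.

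**Step 3. Is the arm contrast biased?** T1 precedes the intervention and the same recall applies in both arms, so randomization should balance it. In a simulation with 43 per arm, complete data, no true effect and 10,000 runs, the mean arm difference in change lay between −0.0024 and +0.0017 SD for r = 0, 0.2, 0.3, 0.5 and 0.7. That is zero within simulation error.

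**Step 4. Precision.** Let r be the correlation of T1 with follow-up, with equal variances at the two times. Take the variance of the arm difference in follow-up score alone as 1.

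- Difference in change (the group-by-time contrast with T1 as a level): 2(1 − r).
- Follow-up adjusted for T1 as a covariate: 1 − r², ignoring a small loss from estimating the slope.
- Ratio of the second to the first: (1 − r)(1 + r) / [2(1 − r)] = (1 + r)/2.

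| r (assumed) | change | covariate | ratio (1 + r)/2 |
|---|---|---|---|
| 0 | 2.0 | 1.0 | 0.50 |
| 0.2 | 1.6 | 0.96 | 0.60 |
| 0.3 | 1.4 | 0.91 | 0.65 |
| 0.5 | 1.0 | 0.75 | 0.75 |
| 0.7 | 0.6 | 0.51 | 0.85 |

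The simulated variances agree with the change column. At r = 0.2, for example, 0.0763/0.0473 = 1.61. The ratio is below 1 for every r below 1, and the gain is largest where r is low.

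**The case against.** The share of days is not the content of the score. Any occurrence in the window counts, so a symptom that began with the stroke before T1 is already recorded at T1. The Exclusion criteria also remove patients with suspected pre-stroke cognitive impairment and with mental disorders, which makes a large pre-stroke contribution less likely. This stands. A reader might infer that the T1 score mostly describes life before the stroke, but the documents support that only for the calendar window. What survives is that T1 holds at most about two weeks of post-stroke time and T2 a full month, so the two scores are still not like for like.

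A reader might also infer that T1 is invalid as a baseline or that the arm comparison is biased. Step 3 shows otherwise for complete data. Data analysis does carry the last value forward, so a patient lost before T2 would contribute the T1 score as the outcome. For that to bias the contrast, early loss must differ by arm and the mean must shift from T1 to T2. The documents give neither quantity, so this limits the reassurance but does not establish a bias.

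Three more objections hold in part:

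- The documents give no correlation between T1 and follow-up. A low r is plausible here but not shown, so the variances are given over a range.
- Data analysis does not name the contrast from which the NPI-Q arm effect will be read. The 2(1 − r) cost applies if it is the group-by-time contrast. As a covariate, a weak T1 helps less but does not add noise beyond the small loss noted in Step 4.
- Entry is limited to under 14 days, but T1 is tied to the programme start and nothing caps the time from onset to T1. A claim that the pre-stroke share always exceeds half is therefore not secured.

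Assessor instructions might anchor the T1 recall differently. They are not shown, and the article states the one-month period without exception.

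**Conclusion.** The mismatch is in the text and the point holds in limited form. For T1 on days 1–13, about 54% to 97% of the NPI-Q window is pre-stroke and the share varies by patient, while T2 and T3 are wholly post-stroke. The T1-to-T2 time effect and within-arm change should therefore not be read as change in post-stroke symptoms.

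The randomized contrast is not biased by this with complete data. Its precision suffers if T1 enters as a time level, the arm effect is read as a difference in change, and r is low. Using T1 as a covariate multiplies that variance by (1 + r)/2, which is 0.60 at r = 0.2 and 0.75 at r = 0.5. These figures rest on assumed r and equal variances. Severity is minor: one secondary outcome is affected, and the primary outcome is not.

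**What to change.** For the NPI-Q, compare the arms at T2 and T3 with the T1 score as a covariate only, not as the first level of the repeated measures. State that within-arm change from T1 and the T1-to-T2 time effect will not be interpreted as change in post-stroke symptoms.

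This takes a sentence or two in Data analysis and no change to data collection. The price is that the NPI-Q is modelled differently from scales that keep T1 as a time level, unless the covariate approach is adopted for all of them.

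Changing the T1 question to symptoms since onset is optional and not required. It would remove symptoms confined to pre-stroke days. But it gives a short window whose length varies by patient and still differs from T2 and T3, and it departs from the instrument as described, so the quoted reliability figures would not apply exactly to T1.

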### Safety outcomes

Fall is a sudden, involuntary, or unintentional fall to the ground or other lower surface not caused by a violent blow, loss of consciousness, sudden paralysis, or seizure [44]. Fall rates are usually expressed per 1,000 bed days. In rehabilitation hospitals where patients are encouraged to mobilize, fall rates typically range from 3 to 16 per 1,000 bed days [45].

For an overview of the study schedule, see Table 1.

**Table 1. t0001:** Schedule of enrolment, interventions and assessments according to the standard protocol items: Recommendations for interventional Trials (SPIRIT).

[figure not shown]					

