#### Exclusion criteria

Patients currently participating in other cognitive interventions;Patients suspected of cognitive impairment before stroke (screening with AD8);Significant aphasia or severe cognitive impairment, inability to understand or cooperate with assessment and treatment instructions;Complicated with severe cardiopulmonary diseases, mental disorders, multiple organ failure, malignant tumors, or seizures.

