### Monitoring

To enhance patient adherence and ensure the effectiveness of the trial, researchers will establish a rapport with patients during communication, inquiring about their level of enthusiasm for participation. Patients will be informed that after discharge, they will need to watch the training videos at home and check in using the ‘Jielong Butler’ WeChat applet. To verify the authenticity of each training session, patients will be required to upload three photos showing their ongoing training activities. These photos will be submitted by the patients’ family members and reviewed by the research team to ensure compliance. This process will also ensure that patients are accompanied by their family members during the exercises. Additionally, patients who consistently complete the check-ins for 8 weeks will receive a small gift as an incentive. After these details are communicated to the patients and their families, the written informed consent will be obtained, and the contact information of the patients and their families will be recorded for follow-up and monitoring.

Data collectors received standardized training on questionnaire evaluation, mastering the content, assessment methods, and techniques while remaining unaware of the study’s group assignments. During data collection, they refrain from guiding or suggesting responses to participants, and the intervention will not be mentioned during assessments to maintain objectivity and consistency. Two university researchers are responsible for data entry and verification to ensure accuracy.

Although the intervention is non-invasive, adverse events such as falls or fractures may occur. To ensure safety, patients and their families will be provided with staff contact information *via* phone or WeChat, and instructed to contact staff immediately if any adverse events occur. Details of all adverse events will be recorded during the trial in the case report forms (CRFs). The ethics committee will examine any connections between adverse events and the intervention and decide whether the study should continue.

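### The only defined safety outcome leaves out falls due to syncope, sudden new paralysis or a seizure, so the reported fall incidence can understate harm

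*Protocol article*

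**What the plan says.** Under Safety outcomes, the protocol article defines a single event. A fall is an unintended descent to the ground or a lower surface that was "not caused by a violent blow, loss of consciousness, sudden paralysis, or seizure". The definition carries a literature reference. The same paragraph gives a published background figure for rehabilitation hospitals: "fall rates typically range from 3 to 16 per 1,000 bed days".

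Three other sections bear on how the definition is used:

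- Outcomes: "The safety outcome, particularly the incidence of falls, will be monitored throughout the study".
- Data analysis: "A safety analysis will be performed to assess safety outcomes". No event list, effect measure or between-arm comparison is given.
- Monitoring: "adverse events such as falls or fractures may occur". Patients and families are to contact staff at once about any adverse event, and all such events go into the case report forms. Further, "The ethics committee will examine any connections between adverse events and the intervention and decide whether the study should continue".

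**The concern.** A harm outcome should capture the events that a reader would worry about if the intervention were unsafe. Here the definition removes falls by cause, and three of the four excluded causes are medical: syncope, sudden paralysis and seizure. In people within two weeks of a first stroke who take up a standing exercise program, a collapse or a new stroke that brings the patient to the floor is among the falls a safety reader most wants to see.

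At stake is the meaning of the fall result. A low fall incidence in the final report could be read as evidence that the program is safe to practise at home, while the falls that came with a collapse or a new deficit sit elsewhere in the records. This is a rule that the article states, so the point does not depend on detail left to a fuller document.

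**Working it through.** The article states no expected number of falls, so there is no figure to reproduce. The check is a comparison of sections.

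1. **What counts as the outcome.** Safety outcomes defines falls only. Outcomes puts particular weight on falls. No other safety outcome is defined, although the word used in Outcomes leaves room for others.

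2. **What the definition removes.** Four examples, read literally:
   - A participant loses balance, tires or trips during a Tai Chi step and falls: counted.
   - A participant faints and falls: not counted.
   - A new stroke causes sudden paralysis and the participant falls: not counted.
   - A seizure causes the fall: not counted.

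3. **What happens to the removed events.** They are adverse events under Monitoring, so they are reported, recorded and open to ethics committee review. Monitoring also names falls without any restriction on cause. The trial therefore holds two sets of falls: all falls, as adverse events, and the restricted set, as the defined outcome. Data analysis refers to safety outcomes and does not say whether the wider set is also summarised.

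4. **Whether eligibility makes the exclusion empty.** Entry requires an NIHSS score below 5 and limb strength above level 3, and the exclusion criteria include "Complicated with severe cardiopulmonary diseases, mental disorders, multiple organ failure, malignant tumors, or seizures". This lowers the chance of the excluded causes at entry. It does not prevent a new stroke, a faint or a first seizure during the twelve weeks.

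5. **Size.** Write N for falls of any cause in an arm and s for the share with an excluded cause. The definition drops s × N falls.
   - N: the only rate in the article is 3 to 16 per 1,000 bed days. With 43 patients followed for 12 weeks (84 days) and no dropout, exposure is 43 × 84 = 3,612 patient-days. At the quoted rates this gives 3.612 × 3 = 10.8 to 3.612 × 16 = 57.8 falls per arm. But this is an inpatient rate for rehabilitation hospitals, and the participants spend part of the period, probably most of it, at home. The range is not a forecast for this trial.
   - s: the article gives no breakdown of falls by cause.
   - With s unknown and N not transferable, s × N cannot be estimated.

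**The case against.** The strongest reply has four parts.

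First, the definition is referenced and has a rationale: it separates ordinary falls from syncope, stroke and seizure, which are adverse events in their own right, and it keeps the fall rate comparable with published figures. This stands as a reason to keep the restricted count as a subset. It does not make that count the best sole safety outcome for this population.

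Second, nothing is lost, because Monitoring captures all adverse events. This also stands. A reader might infer that someone who collapses during training has had no safety event at all; the Monitoring section contradicts that, and such an event could even lead to the study being stopped.

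Third, a reader might infer that these falls are left out of the comparison between arms. The article does not say so: Data analysis specifies no such comparison and does not confine the safety analysis to the defined fall. Nor is every fall connected with a recurrent stroke or a collapse excluded, only those produced by the listed causes.

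Fourth, a reader might suppose that unblinded staff decide the cause, so that the exclusion works differently by arm. No section says who classifies falls. Outcome evaluators, statisticians and data collectors are described as unaware of allocation, and the article does not say whether the staff who receive event reports are. The inference has no textual basis and is not part of this point.

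**Conclusion.** The point holds in a limited form. The one safety outcome that the article defines omits falls caused by syncope, sudden paralysis or seizure, so the fall incidence can understate harm in early post-stroke patients who exercise in hospital and then at home. The events remain visible as adverse events.

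This rests on a literal reading of the definition and on no second safety outcome being defined. That much of the training takes place at home is a reasonable reading of the intervention description, although the article does not state the split. The number of falls affected cannot be derived from the documents, and neither can any effect on a difference between arms. The importance is modest: a cheap improvement to a harm outcome, with no bearing on the primary analysis.

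**What to change.** - Make the safety outcome falls of any cause.
- For each fall, record the suspected cause and whether it happened during a training session, as descriptors and not as conditions for counting.
- Report the falls that meet the present definition as a subset, for comparison with published rates.
- Tabulate by arm the adverse events already recorded, including fractures.

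The cost is a change of wording, two descriptors on the fall record and one extra table. Because details of all adverse events already go into the case report forms, no new assessment is needed. The all-cause total will be slightly less comparable with published fall rates, which the subset covers.

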## Patients and methods

### Study design and setting

This is a 2-group parallel, single-site, single-blind, hospital and home-based randomized controlled trial. Patients with AIS will be recruited from a Hospital in Zhejiang Province. The study consists of an 8-week intervention and a 4-week follow-up (Figure 1). All patients will provide written informed consent in accordance with the 2018 version of the Declaration of Helsinki.

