**Figure 2. F0002:**
[figure not shown]
TC-AOT combined with SOT therapy flow chat.

The AOT video selects the 8 Trigram 5 Steps TC released by the General Administration of Sports of China, and the sensory observation video was recorded by the researchers ourselves. The sensory observation for both the upper and lower limbs involved quick tapping with a wooden board (20s), brushing with silk (20s), and brushing with a cotton swab (20s).

In the hospital, the training will be conducted in the neurology ward. The intervention schedule will run from Monday to Friday, with one session in the morning (10:30–11:00) and three sessions in the afternoon (15:00–15:30, 15:45–16:15, and 16:30–17:00). Patients will be required to participate in only one session per day. After discharge, the researchers will send the videos to the patients and provide daily reminders from Monday to Friday to watch and imitate the videos. During the home-based intervention, a caregiver will accompany the patient throughout the entire video-guided training session and take three photos capturing the patient actively engaged in the intervention. These photos will be uploaded *via* the “Jielong Butler” WeChat applet as evidence of participation. Participants are required to complete this check-in five times per week. The total duration of the intervention will be 8 weeks.

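### Falls are described only by an inpatient metric, bed days, in a trial spent mostly at home, and fall capture could differ between the arms

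*Protocol article*

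**What the plan says.** The design is a "single-blind, hospital and home-based randomized controlled trial" (Study design and setting), and "The study consists of an 8-week intervention and a 4-week follow-up". Under Outcomes, "The safety outcome, particularly the incidence of falls, will be monitored throughout the study".

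The Safety outcomes section defines a fall and then gives one metric and one reference range: "Fall rates are usually expressed per 1,000 bed days", and in rehabilitation hospitals "fall rates typically range from 3 to 16 per 1,000 bed days". No other fall metric appears in the article. Data analysis promises a safety analysis without naming a rate or denominator.

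For reporting, the Monitoring section gives patients and families staff contact details and has them "instructed to contact staff immediately if any adverse events occur". All adverse events go into the case report forms, and the ethics committee reviews their connection with the intervention.

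Contact after discharge is described differently for the two arms. Under Interventions, both receive education and follow-up from the medical and nursing team, at a frequency that is not stated. In the intervention arm, in addition, "the researchers will send the videos to the patients and provide daily reminders from Monday to Friday", a caregiver is present at each home session, and photo check-ins are due five times a week. Randomization and blinding states that participants and those delivering the intervention cannot be blinded.

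**The concern.** There are two separate problems.

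**Metric.** A bed-day denominator stops at discharge, whereas the stated monitoring period does not. Someone applying the printed metric has two choices. Dividing all falls by bed days overstates the rate. Counting inpatient falls only leaves out the period in which most of the exercise takes place. The reference range also comes from rehabilitation inpatients, whereas this trial enrols patients with an NIHSS score below 5 and limb strength above level 3, who then go home.

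**Capture.** When falls reach the team mainly because a patient or relative chooses to report them, an arm with more frequent contact and a caregiver watching each session may report a larger share of its falls. That would affect the comparison between arms, not only the level of the rate.

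Falls are the only safety outcome the article defines, and no data monitoring committee is planned. The continuation decision therefore rests on the recorded events.

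**Working it through.** The article states no expected number of falls and no fall rate for this trial, so there is no figure of its own to reproduce.

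**Inputs from the article.** Follow-up is 8 + 4 = 12 weeks, or 84 days. There are 43 patients per arm (Sample size calculation).

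**Input not in the article.** Length of stay after enrolment is not given. I assume 7 to 14 days and show 5 to 21 days as a wider range.

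**Person-days per arm** with complete follow-up: 43 × 84 = 3,612.

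**Bed days per arm** = 43 × stay. **Share at home** = 1 − stay/84. **Overstatement if all falls are divided by bed days** = 84/stay.

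| Assumed stay (days) | Bed days per arm | Share of follow-up at home | Overstatement |
|---|---|---|---|
| 5 | 215 | 94.0% | 16.8 |
| 7 | 301 | 91.7% | 12.0 |
| 14 | 602 | 83.3% | 6.0 |
| 21 | 903 | 75.0% | 4.0 |

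Home time exceeds half of follow-up whenever the stay is below 84/2 = 42 days, so the statement that the trial is mostly at home does not depend on the exact stay. Counting inpatient falls only would leave out 83% to 92% of follow-up for a 7- to 14-day stay.

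**Effect of the denominator on the comparison.** The factor 84/stay applies to each arm. If stays are similar, it cancels in the rate ratio.

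**Effect of unequal capture on the comparison.** Suppose the true fall rate is constant and equal in both arms, and every inpatient fall is captured. Suppose also that home falls are captured at 90% in the intervention arm and at 70% or 50% in the control arm. These shares are illustrative and nothing in the article supplies them. The apparent rate ratio is (stay + home days × 0.90) / (stay + home days × control share):

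- 7-day stay, 70%: (7 + 77 × 0.90)/(7 + 77 × 0.70) = 76.3/60.9 = 1.25
- 7-day stay, 50%: 76.3/(7 + 77 × 0.50) = 76.3/45.5 = 1.68
- 14-day stay, 70%: (14 + 70 × 0.90)/(14 + 70 × 0.70) = 77/63 = 1.22
- 14-day stay, 50%: 77/(14 + 70 × 0.50) = 77/49 = 1.57

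The extra contact is described only for the 8-week programme. If the capture difference also ends there, and both arms have the control share in the last 28 days, the ratios shrink. For the 7-day stay (49 home days within the programme):

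- 70%: (7 + 44.1 + 19.6)/60.9 = 70.7/60.9 = 1.16
- 50%: (7 + 44.1 + 14)/45.5 = 65.1/45.5 = 1.43

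**The case against.** The strongest reply is that the bed-day sentence is background. It states what is usual and does not say that this trial will divide by bed days. The trial's own commitment is to monitor falls throughout, and a full protocol or analysis plan may supply the denominator and model. This stands in part: the article does not bind the trial to bed days. But bed days are the only metric it offers, and that metric cannot cover the monitoring period it states. That is a mismatch within the document, not merely detail left for later.

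Several stronger readings are tempting and are not supported:

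- **That the fall comparison will be distorted.** A shared bed-day denominator does not bias the ratio between randomised arms with similar stays. Only unequal capture could, and its size is unknown.
- **That the hospital range sets an acceptable number of falls.** Applied to 86 × 84 = 7,224 person-days it would correspond to about 22 to 116 falls, but nowhere is it made an acceptance limit.
- **That collection is purely passive.** Both arms have follow-up and the T2 and T3 assessments, and the assessment schedule in Table 1 is not shown, so scheduled fall questions cannot be ruled out. The reporting instruction makes no distinction between arms. The reminders and check-ins serve adherence and are not said to ask about falls.
- **That falls are the only safety information.** They are the only defined safety outcome, but all adverse events are recorded and fractures are mentioned.
- **That "The outcome measures in this study are all continuous variables" misclassifies falls.** The sentence leads into the repeated-measures analysis of the scales, and safety has its own sentence. At most the wording is loose.

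**Conclusion.** The concern holds in a limited form, and the change should be made. The printed metric and reference range are inpatient ones and do not cover the home period, which is most of the 12 weeks for any stay under 42 days. Dividing all falls by bed days would overstate the rate about 6- to 12-fold for an assumed 7- to 14-day stay, equally in both arms if stays are similar.

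The risk of unequal capture is separate. It follows from the reporting route and the contact pattern as described. The illustrative ratios of about 1.2 to 1.7 with no true difference show only that the effect could matter. They rest on assumed capture shares and are smaller if the difference ends with the programme.

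**What to change.** 1. State in Safety outcomes that falls will be expressed per 1,000 person-days from randomisation to week 12, by arm. Report a rate ratio with its 95% confidence interval and the proportion of patients with at least one fall.
2. Do not use the range of 3 to 16 per 1,000 bed days as a reference for the home period.
3. At T2 and T3, ask every patient and caregiver in both arms the same structured fall question covering the time since the previous assessment. Word it without mention of the exercises, so that the blinded evaluators can ask it.
4. Base the between-arm comparison on those answers. Keep spontaneous reports for safety oversight.

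The visits already take place, and caregivers are already interviewed for the neuropsychiatric questionnaire. The cost is one added question, a few sentences of analysis text and some recall error over intervals of about eight and four weeks.
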